## Study population

Participants will be recruited on a voluntary basis from a group of cigarette smokers who have been clinically diagnosed with T2D. Only patients who smoked daily for at least 5 years will be considered for inclusion in the study. To confirm the smoking status of potential participants, an exhaled carbon monoxide (eCO) measurement will be taken at the screening visit. The cutoff for confirmation as a smoker will be an exhaled CO level greater than or equal to 7 parts per million (ppm). To avoid including patients with poorly controlled diabetes requiring immediate modification of therapy, it was decided to set a glycated hemoglobin percentage of between 6 and 12% as an inclusion criterion. Another criterion is a BMI between 17.6 kg/m^2^ and 34.5 kg/m^2^ to achieve greater homogeneity of the group and to avoid subjects with morbid obesity and coexisting other metabolic disorders, which could affect the outcome of the study. Each participant identified as a smoker with T2D will be offered access to free smoking cessation programs aimed at helping participants quit smoking. Only those who refuse to participate in the smoking cessation programs and express willingness to switch to C-F NA will be eligible for randomization. Before randomization, participants will provide informed consent.

Participants will be required to satisfy all of the following criteria.

Inclusion criteria:Men or women diagnosed with T2D (as defined by the American Diabetes Association).Cigarette smokers of ≥ 10 cigarettes/day (max 30 cigarettes/day).History of regular smoking for at least 5 consecutive years.Verified smoking status (eCO ≥ 7 ppm).Willingness to switch to a C-F NA.Refusal to participate in smoking cessation programs.Glycated hemoglobin between 6 and 12%.Body mass index between 17.6 kg/m^2^ and 34.5 kg/m^2^, both inclusive.Body weight exceeding at least 50 kg (men) or 40 kg (women).

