### Study design

The study follows a randomized controlled design with two parallel groups: control (A) and intervention (B) (Fig. 1). The study will be conducted in seven locations across four different countries (UK, Italy, Poland, and Moldova). The setting for the study will be an ambulatory (outpatient) setting. The design of the trial follows the rules set by the Standard Protocol Items: Recommendations for Interventional Trials (SPIRIT) guidelines (SPIRIT checklist).

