**Fig. 1 Fig1:**
[figure not shown]
Study design flow of DiaSmokeFree; *V* visit, *C-F NA* combustion-free nicotine alternatives

Participants will attend a screening visit within 28 days prior to study visit 1 (Tables 1 and 2). During the screening visit, socio-demographic data, detailed medical history (including medication use), and detailed history of smoking, vaping, and heated tobacco products (HTPs) use will be collected. Additionally, participants’ intention to quit smoking will be assessed. All patients will be offered a smoking cessation program according to the local guidelines. A second opportunity to enroll in a free smoking cessation program will be offered before study enrollment. Any participant who expresses the intention of booking for the cessation program or to quit smoking in the next 6 months will be urged to do so and not be recruited in the study. Patients taking part in the study will be informed that they are free to quit smoking and withdraw from the study at any time. Moreover, participants will be encouraged to quit smoking at every contact time point throughout the whole study.

**Table 1 Tab1:** Study assessments (Control group—Arm A)

Procedure	Screen (V0)	Baseline (V1) day 1	Week 12 (V2) day 90 ± 5	Week 24 (V3) day 180 ± 7	Week 52 (V4) day 360 ± 7	Week1 04 (V5) day 720 ± 7
Eligibility criteria check	X	X				
Medical Hx	X					
Medication use		X	X	X	X	X
Smoking/vaping Hx	X					
Cigarette consumption	X	X	X	X	X	X
Exhaled CO		X	X	X	X	X
FTND		X				
Intention to quit	X	X				
Informed consent		X				
Randomization		X				
Tracker APP installation		X				
Vital signs		X	X	X	X	X
Weight, BMI, waist circumference		X	X	X	X	X
Body composition equation*		X	X	X	X	X
QoL questionnaire		X	X	X	X	X
Smoking cessation advice	X	X	X	X	X	X
Spirometry		X				X
Metabolic syndrome assessment**		X	X	X	X	X
Blood sample***		X	X	X	X	X
Testosterone (men only)		X	X	X	X	X
Urine albumin to creatinine ratio (ACR)						
Safety reporting		X	X	X	X	X

*BL* baseline, *V* visit, *Hx* history, *CO* carbon monoxide, *BMI* body mass index, *FTND* Fagerstrom Test for Nicotine Dependence, *QoL* quality of life, *CBC* complete blood count, *WBC* white blood cells, *Hb* hemoglobin, *LDL* low-density lipoprotein, *HDL* high-density lipoprotein, *HbA1*_*C*_ glycated hemoglobin, *AE/SAE* (serious) adverse incidents

*Body composition (fat and skeletal muscle mass) by validated equation by Lean ME et al. (1996) and Al-Gindan YY et al. (2014)

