*BL* baseline, *V* visit, Hx history, *CO* carbon monoxide, *BMI* body mass index, *FTND* Fagerstrom Test for Nicotine Dependence, *QoL* quality of life, *CBC* complete blood count, *WBC* white blood cells, *Hb* hemoglobin, *LDL* low-density lipoprotein, *HDL* high-density lipoprotein, *HbA1*_*C*_ glycated hemoglobin, *AE/SAE* (serious) adverse incidents, *C-F NA* combustion-free nicotine alternatives

*Body composition (fat and skeletal muscle mass) by validated equation by Lean ME et al. (1996) and Al-Gindan YY et al. (2014)

**Metabolic syndrome is defined according to the National Cholesterol Education Program (NCEP) criteria as having ≥ 3 of the following five features:

1—fasting plasma glucose ≥ 6.1 mmol/L (110 mg/dL)

2—blood pressure ≥ 130/ ≥ 85 mmHg or treatment for hypertension

3—triglycerides ≥ 1.69 mmol/L (150 mg/dL) or treatment for high triglycerides

4—high-density lipoprotein (HDL) cholesterol < 1.29 mmol/L (50 mg/dL) for females or < 1.04 mmol/L (40 mg/dL) for males or treatment for low HDL

5—waist circumference ≥ 88 cm (35 in) for females or ≥ 102 cm (40 in) for males

***To measure: CBC (WBC Hb, platelets), lipid profile (Triglycerides, LDL and HDL cholesterol) HbA1_c_, insulin level

On day 1, baseline assessments will be performed for all participants (Tables 1 and 2). This includes measurements and evaluations related to cardiovascular risk factors, metabolic homeostasis, and general health. Following the baseline assessments, participants will be randomly assigned to either the control (A) arm or the intervention (B) arm. The randomization sequence will be computer generated, with an allocation ratio of 1:2 (arm A:arm B) to account for the estimated 50% proportion of subjects achieving sustained reduction in cigarette consumption of at least 80% in the arm B (see “Statistical Considerations”).

Participants randomized into the intervention arm (B) will be allowed to choose a preferred C-F NA (e-cigarettes, HTPs, etc.) from a given pool of popular options present in the respective markets. They will receive training and counseling on how to use the chosen device and will be provided with a full 2-week supply of the required consumables (cartridges/pods or e-liquids refill bottles for e-cigarettes, tobacco sticks for HTPs) on day 1. Participants randomized into the control arm (A) will be offered the usual standard of care, which includes brief smoking cessation counseling at each visit.

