#### Statistical analyses

The primary end point for the statistical analysis will be the between-groups difference in the calculated prevalence of MetS after at least 24 months of follow-up. The full analysis set (FAS) will include all subjects randomized to the intervention arm who achieve a sustained reduction in cigarette consumption of at least 80% during the follow-up, combined with all subjects randomized into the usual standard of care control group. Two approaches to the primary analysis will be used: (a) unadjusted analysis, based on a direct comparison of the change in prevalence using a Z test, and (b) adjusted analysis, where potential confounders (including age, gender, smoking, and medications for hypertension, hyperlipidemia, or diabetes) will be analyzed to identify factors that may influence the primary outcome. A generalized linear model will be used to adjust for identified confounders. Any difference between the groups will be assessed for statistical significance at a two-sided alpha of 0.05.

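### In the analysed set, Arm B is kept by switching success but the primary Z test is pooled over four countries, so country differences can confound a comparison of 24-month MetS prevalence

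*Protocol article*

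**What the plan says.** All references are to the protocol article.

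- **Test.** Statistical analyses gives two approaches to the primary analysis. Approach (a) is an "unadjusted analysis, based on a direct comparison of the change in prevalence using a Z test". Approach (b) is a generalized linear model, for which "potential confounders (including age, gender, smoking, and medications for hypertension, hyperlipidemia, or diabetes) will be analyzed to identify factors" that may influence the outcome. Neither names country or site.
- **Analysed set.** The same section builds the full analysis set from all controls plus only those Arm B patients who sustain a reduction in cigarette consumption of at least 80%.
- **Countries.** Study design lists seven locations in the UK, Italy, Poland and Moldova. Allocation is computer generated at 1:2, and the article mentions no stratification by country. Arm B patients choose a product "from a given pool of popular options present in the respective markets".
- **Outcome.** The footnotes to Tables 1 and 2 count drug treatment towards three of the five MetS features: blood pressure, triglycerides and HDL.
- **Quantity tested.** Objectives and end points defines the primary end point as a change between baseline and 2 years. Statistical analyses opens with the between-group difference in prevalence after at least 24 months, then describes a Z test on the change in prevalence. Both readings are open.

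**The concern.** Randomisation balances country between the arms as allocated. It does not balance country between all controls and the Arm B patients who switched. Countries where switching succeeds more often supply a larger share of the analysed Arm B, while the controls keep the country mix they were randomised with.

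Switching may plausibly differ by country because the product pool follows the local market. MetS prevalence may differ because treated features count and prescribing practice varies. If both differ, analysed Arm B and the controls have different expected prevalence even when the products do nothing. A pooled, unadjusted test would attribute that gap to treatment. The gap could create an apparent benefit or hide a real one.

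**Working it through.** **1. The plan's own figures.** Inputs from Powering and sample size calculation: MetS 70% v 55%, two-sided 5%, power 80%.

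- n per arm = (1.96 + 0.84)² × (0.70×0.30 + 0.55×0.45) / 0.15² = 159.6, which rounds up to the stated 160.
- Total = 160×1.2 + 320×1.2 = 192 + 384 = 576, as stated.
- After 20% withdrawal: 192×0.8 = 153.6 controls and 384×0.8 = 307.2 in Arm B. Half of the latter switch, leaving 153.6 in the analysed Arm B.

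**2. Assumptions.** The article gives no country-specific rates. The check takes four equal countries, mean MetS 70%, mean switching 50% and no treatment effect. It also assumes that, within a country, switchers and non-switchers have the same MetS prevalence.

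**3. Formula.** With country prevalence m and switching rate r:

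spurious gap = Σ(r·m)/Σr − mean(m)

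Example: m = 0.50, 0.633, 0.767, 0.90 and r = 0.70, 0.567, 0.433, 0.30.

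- Σ(r·m) = 0.350 + 0.359 + 0.332 + 0.270 = 1.311, and Σr = 2.0.
- Analysed Arm B prevalence is 65.55%, against 70% in controls: a gap of −4.45 points.

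**4. Simulation.** 20,000 trials per row, with 154 controls and 307 retained Arm B patients reduced to switchers.

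| MetS by country | Switching by country | Gap (points) | Type I error, pooled Z | Type I error, country-stratified CMH |
|---|---|---|---|---|
| 60–80% | 50% everywhere | 0 | 5.2% | 5.2% |
| 60–80% | 60–40% | −1.1 | 5.3% | 4.6% |
| 60–80% | 70–30% | −2.2 | 7.1% | 5.2% |
| 50–90% | 70–30% | −4.45 | 13.3% | 4.9% |
| 50–90% | 30–70% (same order) | +4.45 | 14.2% | 5.2% |

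An analytic check on an intermediate case: m = 0.85, 0.75, 0.65, 0.55 and r = 0.30, 0.40, 0.60, 0.70.

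- Analysed Arm B prevalence = 1.33/2.0 = 66.5%, a gap of −3.5 points.
- SE = √[(0.665×0.335 + 0.70×0.30)/153.6] = 0.053, so the shift is 0.035/0.053 = 0.66 standard errors.
- Rejection = P(Z > 1.30) + P(Z < −2.62) = 0.097 + 0.004 = 10.1%.

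**5. All randomised patients.** In the same scenarios without selection of Arm B, the mean difference is about 0 and the pooled Z test rejects in 4.8% to 5.0% of trials. With a true 15-point difference (154 v 307), stratifying by country raises power from 88.4% to 89.9% (MetS 55–85%) or from 88.2% to 91.4% (MetS 50–90%). That is a gain of 1.5 to 3.2 points, under wide spreads.

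**6. Change from baseline.** If each country's prevalence is stable over time, the expected change is zero in every country. The gap is then Σ(r·0)/Σr − 0 = 0 whatever the switching rates. Simulating the 55–85% case this way gave a gap of 0.0 points and rejection of 4.8% to 5.4%.

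**The case against.** Four arguments can be made against the point.

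- **The tested quantity may be change.** Stable country differences then cancel within each arm, and confounding would need time trends that differ by country. This stands, and it limits the point to the prevalence reading. It does not remove the point, because the opening sentence of Statistical analyses describes a prevalence difference at follow-up.
- **The article is condensed and the SAP is not shown.** A country term is often left to the SAP, and the covariate list is open-ended. This stands for approach (b). Medications are also already candidates there, which partly covers local prescribing. It does not answer approach (a), where an unadjusted test is a stated choice.
- **The sizes rest on assumed rates.** The larger figures need wide spreads in switching and in MetS, in a strict order across countries. This is true: with moderate spreads the error rate stays near 5%.
- **The real cause is the analysis set.** This also stands. Stratifying removes only the between-country part of the selection.

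A reader might go further and infer that pooling countries with local products and local cessation programmes is itself enough to produce a false effect. The article does not support that. Local products can make the effect vary by country, but they do not by themselves create one. On cessation, "All patients will be offered a smoking cessation program according to the local guidelines", which applies to both arms before allocation, and "Only those who refuse to participate in the smoking cessation programs and express willingness to switch to C-F NA will be eligible for randomization". Later referral is offered to both arms as well.

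**Conclusion.** The point holds in a limited form. The analysed set lets Arm B's country mix drift from that of the controls, and the stated pooled, unadjusted Z test does nothing about it. For a comparison of 24-month prevalence, the spurious difference is about 1 to 4.5 points in either direction under the assumed ranges. At the upper end that is 4.45/15, or about 30% of the target effect. Type I error runs from about 5% to 14%.

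This requires both switching success and MetS prevalence to differ by country, which the article neither states nor excludes. The bias is zero if switching is equal across countries or if all randomised patients are compared. It is also zero for stable country differences if change from baseline is tested. Among all randomised patients, the case for a country term is precision alone.

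**What to change.** - In approach (a), replace the pooled Z test with a Mantel-Haenszel risk difference and a CMH test, both stratified by country.
- In approach (b), enter country as a fixed, pre-specified term in the generalized linear model, not as a candidate to be identified from the data.
- State whether the primary contrast is 24-month prevalence or change from baseline. The stratified procedure above is for 24-month status.

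The cost is revised wording and slight extra analysis work, with no new data. In the scenarios above the stratified test kept type I error at 4.6% to 5.2%, but those scenarios assume no selection within countries. Where switchers differ from non-switchers in the same country, stratifying will not help. The definition of the analysis set therefore needs its own correction, and a country term should not be presented as a substitute for it.

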**Metabolic syndrome is defined according to the National Cholesterol Education Program (NCEP) criteria as having ≥ 3 of the following five features:

1—fasting plasma glucose ≥ 6.1 mmol/L (110 mg/dL)

2—blood pressure ≥ 130/ ≥ 85 mmHg or treatment for hypertension

3—triglycerides ≥ 1.69 mmol/L (150 mg/dL) or treatment for high triglycerides

4—high-density lipoprotein (HDL) cholesterol < 1.29 mmol/L (50 mg/dL) for females or < 1.04 mmol/L (40 mg/dL) for males or treatment for low HDL

5—waist circumference ≥ 88 cm (35 in) for females or ≥ 102 cm (40 in) for males

***To measure: CBC (WBC Hb, platelets), lipid profile (triglycerides, LDL and HDL cholesterol) HbA1_c_, insulin level

**Table 2 Tab2:** Study assessments (intervention group—Arm B)

Procedure	Screen (V0)	BL (V1)	Wk2	Wk4	Wk8	Wk12 (V2)	Wk20	Wk24 (V3)	Wk32	Wk40	Wk48	Wk52 (V4)	Wk60	Wk68	Wk76	Wk84	Wk92	Wk100	Wk104 (V5)
Eligibility criteria check	X	X																	
Medical Hx	X																		
Medication use		X				X		X				X							X
Smoking/vaping Hx	X																		
Cigarette consumption	X	X	X	X	X	X	X	X	X	X	X	X	X	X	X	X	X	X	X
Exhaled CO		X	X	X	X	X	X	X	X	X	X	X	X	X	X	X	X	X	X
FTND		X																	
C-F NA use			X	X	X	X	X	X	X	X	X	X	X	X	X	X	X	X	X
Intention to quit	X	X																	
Informed consent		X																	
Randomization		X																	
Tracker APP installation		X																	
C-F NA familiarization		X																	
Vital signs		X				X		X				X							X
Weight, BMI, waist circumference		X				X		X				X							X
Body composition equation*		X				X		X				X							X
QoL questionnaire		X				X		X				X							X
Smoking cessation advice	X	X	X	X	X	X	X	X	X	X	X	X	X	X	X	X	X	X	X
Spirometry		X																	X
Metabolic syndrome assessment**		X				X		X				X							X
Blood samples***		X				X		X				X							X
Urine albumin to creatinine ratio (ACR)		X				X		X				X							X
Testosterone (men only)		X				X		X				X							X
Safety reporting		X				X		X				X							X
Provide C-F NA device (+ 2 wks supply of consumables)		X																	
Hand out 2 wks supply of consumables			X																
Hand out 4 wks supply of consumables				X	X		X				X							X	
Hand out 2 × 4 wks supply of consumables						X		X	X	X		X	X	X	X	X	X		
Product use checks (collect used and unused consumables)			X	X	X	X	X	X	X	X	X	X	X	X	X	X	X	X	X

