### Statistical considerations

#### Powering and sample size calculation

The sample size calculation is based on assumptions that the expected reduction in MetS prevalence after smoking cessation is 15% [24–28], and the expected baseline prevalence of MetS in T2D is 70% [29–32]. Sample size was calculated on the basis of demonstration of superiority, assuming a normal distribution of the sample [33]. Significance level was set at 5% (*α* = 0.05), with a power of 80% (*β* = 0.20). Based on these assumptions, the minimum number of subjects with analyzable data required is 160 per treatment arm (N). Considering an estimated 50% proportion of subjects in the intervention arm achieving sustained reduction in cigarette consumption of at least 80% for the study duration [34–38], the final number of subjects required in the intervention arm (N2) is set at 320. Taking into consideration the expected 20% withdrawal rate in both arms over 2 years, the total number of subjects recruited in each treatment arm is increased by this amount. Thus, the total number of subjects for both arms is set at 576.

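### The primary analysis consists of two unranked tests at 0.05; the adjusted one selects its covariates by their link to the outcome, without limiting them to baseline or naming baseline metabolic syndrome

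*Protocol article*

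**What the plan says.** All of this is in the protocol article, under Statistical analyses unless noted.

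- The quantity analysed is the "between-groups difference in the calculated prevalence of MetS after at least 24 months of follow-up".
- Both analyses carry primary status: "Two approaches to the primary analysis will be used". The first, (a), is described as an "unadjusted analysis, based on a direct comparison of the change in prevalence using a Z test"; the second, (b), is adjusted.
- In (b), "potential confounders (including age, gender, smoking, and medications for hypertension, hyperlipidemia, or diabetes) will be analyzed to identify factors" linked to the primary outcome. How these enter the model is stated as follows: "A generalized linear model will be used to adjust for identified confounders".
- On the level of the tests, the section says: "Any difference between the groups will be assessed for statistical significance at a two-sided alpha of 0.05". No order, lead analysis or division of alpha is given.
- The full analysis set (FAS) takes from the intervention arm only those with a sustained cut in cigarettes of at least 80%, and takes all controls.
- In the MetS definition (footnotes to Tables 1 and 2), treatment satisfies three of the five features. The blood pressure feature, for example, is met by the reading in "mmHg or treatment for hypertension", and there are similar clauses for triglycerides and HDL. The glucose feature has no treatment clause.
- Tables 1 and 2 record cigarette consumption and medication use at baseline and at every later clinical visit. MetS is assessed in both arms at baseline.

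**The concern.** Four things are left open at the point where the primary conclusion is drawn.

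1. **No deciding analysis.** If the Z test and the model disagree, nothing says which one counts. If either may be claimed, the error rate is above 5%.
2. **Covariates chosen from the outcome.** The model's content is settled after outcomes are examined, in an open-label trial.
3. **Timing of smoking and medication.** Baseline values would be sound covariates. On-study values would not be. The Methods and the Discussion attribute the expected benefit to avoiding cigarette smoke, so on-study smoking is the mechanism under test. On-study treatment for hypertension, triglycerides or HDL is part of the outcome's own definition.
4. **Baseline MetS not named.** It is measured in everyone and is probably a strong predictor of MetS at 24 months. Leaving it out of the model gives up power at no saving.

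**Working it through.** **Sample size as stated.** Inputs from Powering and sample size calculation: 70% versus 55%, two-sided alpha 0.05, 80% power. With unpooled variance:

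n = (1.960 + 0.842)² × (0.70×0.30 + 0.55×0.45) / 0.15² = 7.85 × 0.4575 / 0.0225 = 159.6, so 160 per group.

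This reproduces the protocol's figure. The calculation is for one unadjusted comparison of two proportions, with no second test and no covariates. The total follows as (160 + 320) × 1.20 = 576, which is 192 and 384 at 1:2.

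**Expected size of the stated FAS.** Controls: 192 × 0.80 = 153.6. Intervention: 384 × 0.80 × 0.50 = 153.6. That is about 154 per group.

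**Two tests at 0.05.** If the tests were independent, the chance of at least one false positive would be 1 − 0.95² = 9.75%. They are correlated, so this was simulated under no effect. The assumptions were 70% prevalence in both groups, six candidate baseline covariates unrelated to arm, and selection into the model at p < 0.05.

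| Setting | At least one test significant |
|---|---|
| 160 per group, both tests on 24-month status | 5.4% to 6.7% |
| 160 per group, (a) on change and (b) on 24-month status | 9.1% to 9.8% |
| About 154 per group | 5.8% to 8.2% |

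Monte Carlo error is about 0.3 points, which is why a value can sit marginally above 9.75%. In the same simulations the adjusted test with selected covariates, taken alone, rejected in 4.8% to 5.3% of runs. The excess therefore comes from having two tests.

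**If smoking meant on-study smoking.** In the stated FAS every intervention subject has at least an 80% reduction. Let q be the share of controls who also reach it; q is an assumption. With equal groups, R² between arm and reduction is (1 − q)/(1 + q), and the variance inflation of the arm effect is 1/(1 − R²) = (1 + q)/(2q).

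| q | R² | Variance inflation | Total difference, 15 × (1 − q) |
|---|---|---|---|
| 0% | 1.00 | arm and reduction inseparable | 15.0 points |
| 5% | 0.90 | 10.5 | 14.25 points |
| 10% | 0.82 | 5.5 | 13.5 points |
| 20% | 0.67 | 3.0 | 12.0 points |

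The last column assumes that the effect acts wholly through the reduction (70% to 55%). Under that assumption the arm coefficient after adjustment is about 0 wherever it can be estimated (q above 0). This shows what the wording would permit. It is not a forecast of what will be done.

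**Baseline MetS as a covariate.** Simulated at about 154 per group, 70% versus 55%, with an assumed correlation between the latent baseline and 24-month variables behind MetS status:

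| Analysis | Power |
|---|---|
| Z test on 24-month prevalence | about 78% to 79% |
| Model with baseline MetS, correlation 0.3 / 0.5 / 0.7 / 0.8 | about 80% / 82% / 88% / 92% |
| Z test on change, correlation 0.3 to 0.5 | about 59% to 67% |
| Z test on change, correlation 0.3 to 0.8 | about 59% to 87% |

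At every correlation tried, the adjusted model has more power than the test of change. Monte Carlo error for power is about 0.5 to 0.8 points.

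**The case against.** An unadjusted result beside an adjusted one is ordinary reporting, and an analysis plan that is not shown may rank the two. Covariate timing is also commonly left to that plan, and baseline smoking measures exist: history, cigarettes per day and the Fagerström score. These points carry weight, and several stronger readings should be resisted.

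- **That the plan adjusts away its own effect.** The text says only smoking, listed with age and gender. It never says on-study smoking. The fall to zero above holds only under that reading and the assumption of complete mediation.
- **That all the listed medication is part of the outcome.** This is true of treatment for hypertension, triglycerides and HDL. It is not true of diabetes medication.
- **That baseline MetS is excluded.** The covariate list is open-ended, so it is unnamed rather than ruled out. Analysis (a) already uses baseline through the change in prevalence.
- **That covariate selection inflates the error rate.** It did not in the simulation, which used baseline covariates independent of arm.
- **That omitting site is a validity error.** The article describes no stratification by site, so site or country is a matter of precision.

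The objection does not remove what the article states outright. Both approaches are called primary, one alpha applies to any difference, and covariates are identified by their influence on the outcome. A plan that fixed the covariates in advance would contradict that last statement, so the wording has to change.

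**Conclusion.** The point holds as a fault in how the primary analysis is fixed. Two unranked primary tests put the either-significant error rate at about 6% to 8%, and at up to about 9.8% if one tests change and the other tests 24-month status. The lack of a rule for discordant results matters at least as much. Outcome-driven selection had no measurable error-rate cost in the setup tried; the objection to it is that the primary estimate should not depend on choices made after outcomes are seen. The silence on timing is a gap that one word closes, but it needs closing because on-study smoking is nearly collinear with arm in the stated FAS. Not naming baseline MetS forgoes roughly 1 to 14 points of power against the unadjusted 24-month comparison (80% to 92% against 78% to 79%). That range rests entirely on assumed correlations of 0.3 to 0.8.

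**What to change.** Before 24-month outcomes are examined by arm, name one primary analysis: a generalized linear model of MetS at 24 months with arm and a fixed list of baseline covariates. The list would be baseline MetS status (or number of features met), age, sex, cigarettes per day, and antihypertensive, lipid and glucose-lowering treatment, all at baseline. Country or site can be added for precision. State that no covariate measured after randomisation enters the model and that none is selected from the data. Report the unadjusted Z test as supportive.

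The cost is wording in the protocol and the analysis plan; Tables 1 and 2 schedule the needed data at screening or baseline. The price is a slightly more model-dependent primary estimate. Baseline adjustment does not repair the FAS's selection of the intervention arm on achieved reduction, which is a separate issue.
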